**Methods:**

The prospective randomised controlled trial will enrol 300 subjects with MCI (age ≥ 60 years). Participants will be randomly assigned to: (a) the experimental group, which will undergo sessions of adapted tango, music therapy, engagement in social activities, cognitive intervention and psycho-education for 6 months or (b) the control group, which will receive psycho-education and advice on healthy lifestyle for 6 months. All outcomes will be analysed before intervention (baseline), immediately after termination (follow-up 1), after 6 months (follow-up 2) and after 2 years (follow-up 3).

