**Fig. 1 Fig1:**
[figure not shown]
Flowchart of strength project

#### Specific aim 1

To study the effect of the multimodal intervention on cognitive performances, functional status, and mobility in MCI subjects by objectively measured parameters (baseline vs. follow-up 1, follow-up 2 and follow-up 3). Mobility (i.e., the ability of a subject to move in his/her environment) is often compromised in elderly people as a consequence of falls and other injuries and this could cause disability and reduced social engagement. The identification of approaches that might prevent motor–cognitive impairment would be a pivotal advancement in the correct management of aging people. Mobility will be evaluated by means of balance, walking test and gait speed; motor–cognitive function, defined as a process of coordination of movements finalized to a particular motor goal, will be measured by means of visual–spatial memory task.

The longitudinal monitoring of cognitive decline and dementia onset will also be implemented (follow-up 2 and follow-up 3).

#### Specific aim 2

To study the effect of the intervention on psycho-social aspects (e.g., psychological well-being, perceived stress, quality of life, metacognition and mood status), lifestyle characteristics and social network (baseline vs. follow-up 1, follow-up 2 and follow-up 3).

#### Specific aim 3

To study the effect of the intervention on specific biomarkers (baseline vs. follow-up 1, follow-up 2 and follow-up 3).

#### Experimental design aim 1

Neuropsychological as well as cognitive and clinical assessment, including cardiovascular, anthropometric, and functional evaluation (e.g., blood pressure, body mass index, ultrasound heart examination through standard echocardiogram, 6-min walk test, gait speed, Berg Balance Scale, handgrip strength, Physical Activity Scale for the Elderly, basic activities of daily living and instrumental activities of daily living) will be carried out (Table 1).

**Table 1 Tab1:** Clinical, functional, and neuropsychological assessment

Instruments
*Cognitive assessment*
Clinical Dementia Rating Scale—CDR [20]
Memory Complaint Questionnaire—MAC-Q [21]
Montreal cognitive assessment—MoCA [22]
Mini mental state examination—MMSE [23]
Rey auditory verbal learning test—RAVLT [24]
Phonological verbal fluency—PVF [24]
Supra-span of Corsi [25]
Semantic verbal fluency—SVF [26]
Attentive matrices [26]
Trail making test A−B—TMT A–B [27]
*Psychological assessment*

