### Randomisation

The selected subjects will be randomly allocated to the experimental group (EG, *n* = 150) or to the control group (CG, *n* = 150) using a randomisation list.

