### Sample size calculation

It was based on the null hypothesis that proportion of “success” and “failure” of the intervention is equal in the two groups (i.e., EG and CG), such as OR = 1.

Success and failure were defined on the basis of significant variation in the primary outcomes. Considering an OR = 1.5 indicative of an effect of the intervention, a total sample of 300 subjects allows us to reach a 90% of statistical power using logistic regression at the 5% level (two tailed). Drop-out rate was set at 20%.

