### Statistical analysis

All data will be collected in a database. A descriptive analysis will be performed to assess the distribution of variables and the presence of possible outliers. The latter will be checked and identified separately and then excluded from the analysis. For normally distributed variables, the comparisons between EG and CG at baseline will be carried out by *t *Student test or Chi-square test, while those between baseline and follow-up phases by paired sample *t* test. For non-normally distributed variables, non-parametric tests will be used. Correlation analysis will be performed to evaluate the relationships among variables and general linear models and repeated measures ANOVA will be used to assess the intervention effects adjusted for confounding variables (e.g., gender, age classes, marital status, schooling, drugs, and other variables that will emerge after analysis of secondary outcomes). The SPSS software will be employed.

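### Run over the four planned visits, repeated measures ANOVA drops every subject with one missed visit; for the continuous outcomes a mixed model would keep the measured data

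*Protocol article*

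**What the plan says.** In the protocol article, the Statistical analysis section states that "general linear models and repeated measures ANOVA will be used to assess the intervention effects adjusted for confounding variables". It adds "The SPSS software will be employed". Besides these two methods, that section lists tests between arms at baseline, paired tests of baseline against follow-up, and correlations. It does not say which visits enter each model.

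The Methods paragraph of the abstract places the measurements at baseline and then "immediately after termination (follow-up 1), after 6 months (follow-up 2) and after 2 years (follow-up 3"). The three specific aims under Study design each set out the comparison "baseline vs. follow-up 1, follow-up 2 and follow-up 3".

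Randomisation has subjects "randomly allocated to the experimental group (EG, *n* = 150) or to the control group (CG, *n* = 150"). Under Sample size calculation, "Drop-out rate was set at 20" per cent, with no timing and no split by arm.

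The primary outcome is binary, a gain of at least 1 point on the Corsi test. The sample size is tied to logistic regression. The secondary outcomes include many continuous scales and biomarkers, and conversion to dementia.

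**The concern.** Repeated measures ANOVA, as run by the SPSS repeated-measures GLM procedure, works on subjects with a value at every visit in the model. With four visits in one model, a subject seen at baseline, follow-up 1 and follow-up 2 but not at 2 years contributes nothing, not even to the comparison at the end of the intervention.

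Two things are at stake:

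- **Precision.** Data already collected are thrown away whenever any visit is missing.
- **Bias.** The Discussion describes the subjects as being at high risk of dementia, so loss linked to decline is plausible over 2 years. The completers may then differ from the randomised subjects, and the contrast between arms may shift.

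The criticism is of a method that the article names. It is not a complaint that missing-data detail is absent.

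**Working it through.** **The plan's own figure.** The article gives no precision or power figure for the ANOVA. Its only such figure belongs to the binary outcome: "a total sample of 300 subjects allows us to reach a 90% of statistical power using logistic regression at the 5% level (two tailed"). The assumed odds ratio is 1.5. For a two-arm comparison with 150 per arm, power at that odds ratio is at most 41.6% (at a control success rate near 0.45), so the 90% is not reproduced. That is a separate problem, and nothing below depends on it.

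**Step 1: complete subjects.** Inputs from the article are N = 300 and 20% drop-out.

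300 × (1 − 0.20) = 240 complete subjects, or 120 per arm if losses are equal.

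**Step 2: follow-up 1 records discarded.** The timing of drop-out is not given, so three assumptions are shown. Records discarded = measured at follow-up 1 − complete. The ratio of standard errors under random loss is sqrt(measured / complete).

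| Lost before follow-up 1 (assumed) | Measured at follow-up 1 | Complete | Discarded | Ratio of standard errors |
|---|---|---|---|---|
| 0% | 300 | 240 | 60 | sqrt(300/240) = 1.12 |
| 5% | 285 | 240 | 45 | sqrt(285/240) = 1.09 |
| 10% | 270 | 240 | 30 | sqrt(270/240) = 1.06 |

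Sixty records and 12% are therefore the upper end, reached when every loss comes after follow-up 1.

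**Step 3: bias by simulation.** All inputs here are assumptions except N and the 20%:

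- 150 per arm, four visits, SD 1, correlation 0.6 between visits.
- True effect of 0.40 SD at every follow-up, or 0.
- Drop-out at two points, after follow-up 1 and after follow-up 2, with probability 0.1056 each, since (1 − 0.1056)² = 0.80.
- Drop-out is either random or driven by the observed change from baseline, with a logistic slope of 1.5 per SD of change. In the arm-specific cases it follows decline in one arm and is random in the other, at the same average rate.

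The complete-case estimate is the difference between arms in change from baseline among subjects with all four visits, which is the contrast the ANOVA uses. The comparator is a likelihood model with unstructured covariance fitted to all observed visits, with baseline among the responses.

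| Drop-out | True effect | Complete-case, follow-up 1 | Complete-case, follow-up 3 | Mixed model, follow-up 1 | Mixed model, follow-up 3 |
|---|---|---|---|---|---|
| Random | 0.40 | 0.40 | 0.40 | 0.41 | 0.39 |
| Same decline rule in both arms | 0.40 | 0.34 | 0.36 | 0.41 | 0.41 |
| Follows decline in CG only | 0.40 | 0.24 | 0.29 | 0.41 | 0.40 |
| Follows decline in EG only | 0.40 | 0.56 | 0.51 | 0.40 | 0.40 |
| Random | 0 | 0.00 | 0.00 | 0.00 | 0.01 |
| Same decline rule in both arms | 0 | 0.00 | 0.00 | −0.01 | 0.00 |
| Follows decline in CG only | 0 | −0.16 | −0.11 | −0.01 | −0.01 |
| Follows decline in EG only | 0 | 0.16 | 0.10 | 0.00 | 0.00 |

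The simulation error of the mixed-model columns is 0.006 to 0.007. Under random drop-out with a true effect of 0.40, the follow-up 1 standard error was 0.111 in completers against 0.100 using all measured subjects. This agrees with Step 2.

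**Step 4: a milder setting with no true effect.** With AR(1) correlation 0.7, covariance adjustment for baseline, an assumed drop-out intercept of −2.5 and about 19% incomplete, the follow-up 1 bias in completers depends on the drop-out slopes (EG/CG):

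- −0.5/−1.3: −0.074 SD
- −0.8/−1.0: −0.02 SD
- −0.9/−0.9: 0.00 SD

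The standard error in this setting is about 0.09, so even the largest of these is below one standard error.

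**The case against.** The strongest objection is that the article never says all four visits enter one ANOVA. It names general linear models beside it, and a general linear model for follow-up 1 alone loses no follow-up 1 data. The aims compare baseline with each follow-up, which also fits a series of two-visit analyses. Under that reading no follow-up 1 record is deleted. This stands, and it makes the point conditional. It does not remove it, because one model over the planned visits is the ordinary use of the named method and nothing in the article rules it out.

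A reader might infer more than the documents support in four ways:

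- **That the trial's estimate will be biased, or that a null effect will look real.** Random drop-out gives no bias, and with no true effect a common rule in both arms gives none either. The null bias needs drop-out that relates to decline differently in each arm.
- **That weekly against monthly contact makes such a difference likely.** That contrast applies only during the 6-month intervention. It has ended before the simulated losses begin, and the Intervention section gives the control group the same clinical monitoring. Subjects lost during the intervention have no follow-up 1 value to discard.
- **That the primary outcome is affected.** It is a binary responder outcome, and the sample size refers to logistic regression. A linear mixed model does not analyse it.
- **That sphericity over unequally spaced visits is a serious further fault.** Corrected and multivariate tests deal with it, so it is minor.

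It is also fair to say that visits per model, covariance structure and sensitivity analyses may be set out in a full protocol or analysis plan not shown here. Their absence is not criticised.

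**Conclusion.** The point holds for the continuous outcomes, on the reading that the planned visits enter one repeated measures ANOVA. At 20% drop-out, about 240 of 300 subjects remain. Between 30 and 60 measured follow-up 1 records are discarded if 10% to 0% of subjects leave before that visit. Loss of precision at follow-up 1 then follows from the method: 6% to 12% in the standard error under random loss.

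Bias is possible but conditional. Under the assumed inputs and a common decline-driven rule, a true 0.40 SD effect is attenuated to about 0.34. Larger shifts in either direction, and any bias when there is no effect, require a rule that differs by arm. The article gives no evidence on whether that will occur. The sizes depend on the assumed correlation, effect and drop-out slope.

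The mixed model recovered the true value in every case because the simulated drop-out depended only on observed scores. It would not by itself correct for loss that depends on unobserved decline. The change is worth making, but the weakness does not invalidate the trial.

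**What to change.** For the continuous outcomes, replace repeated measures ANOVA with a likelihood-based mixed model for repeated measures, using all observed visits of all randomised subjects in their allocated arm:

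- Terms: arm, visit, arm-by-visit, baseline score and baseline-by-visit.
- Unstructured covariance across visits.
- Report the arm contrast at each of follow-ups 1, 2 and 3.
- Add a sensitivity analysis for drop-out that is not at random, for example one that treats loss after decline or dementia as unfavourable. It should also cover subjects with no follow-up visit, who add nothing to the arm contrasts in this model.

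The binary Corsi responder outcome keeps its logistic regression and is outside this change. If separate two-visit analyses were intended instead, the text should say so.

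The cost is a change of wording and slightly more analysis work. SPSS already offers the method (MIXED), and no new data, visits or subjects are needed.

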### Inclusion and exclusion criteria

The inclusion criteria comprise: (a) diagnosis of MCI according to the guidelines of the National Institute of Aging [42]; (b) age 60 years or older, (c) availability during the intervention and testing phases, (d) presence of a caregiver; (e) capability to sign the informed consent.

Exclusion criteria include: (a) presence of sensory-physical deficits that would prevent participation in the study; (b) diagnosis of dementia; (c) presence of serious medical and/or psychiatric conditions.

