#### Primary outcome: success of the intervention

The response to the intervention will be evaluated using performance in the Corsi test [25]: an increase of at least 1 point will indicate a success based on the enhancement of the spatial learning processes.

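### Adjusting the intervention effect for age in classes rather than in years gives up a little precision for no stated reason; it does not bias the result.

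*Protocol article*

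**What the plan says.** The Statistical analysis section of the protocol article states that "general linear models and repeated measures ANOVA will be used to assess the intervention effects", with adjustment for confounders. The examples it gives are "gender, age classes, marital status, schooling, drugs", and the list is left open to further variables. Age is therefore listed as a grouped variable in the models that estimate the effect, not only in descriptive summaries.

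The eligibility criterion for age is "age 60 years or older", with no upper limit. The article gives no cut points, no number of classes and no reason for grouping. Nowhere does it enter age as a continuous term.

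**The concern.** Age is a plausible predictor of cognition, mobility and dementia onset, which are the outcomes of this trial. Adjusting for a prognostic covariate removes outcome variance that has nothing to do with treatment and so sharpens the estimated effect. If age is cut into classes, only the differences between classes are removed. A participant at the bottom of a class and one at the top are treated as the same age, and chance age differences between the arms within a class are not adjusted for.

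What is at stake is precision: slightly wider confidence intervals than the same data could give.

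**Working it through.** **Inputs.** From the article: 300 participants, 150 per arm, 20% drop-out (240 analysed), and age classes as a covariate. Not in the article, hence assumed: a roughly normal age distribution, two to five equal-sized classes, and an age-outcome correlation r of 0.1 to 0.5, with 0.2 to 0.4 as the central range.

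**The plan's own figure.** The article gives none for the value of age adjustment. Its 90% power for an odds ratio of 1.5 concerns a binary outcome analysed by logistic regression. That figure does not reproduce for a two-arm comparison: 150 per arm give at most 41.6%, at a control success rate of 0.45. This is a separate matter, and the present point does not depend on it. Below, 90% serves only as a reference level for expressing the loss.

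**Step 1: share of the age variance that classes keep.** For k equal classes of a standard normal variable with boundaries q, the class means are m_j = k[φ(q_(j−1)) − φ(q_j)], and the share kept is the average of m_j².
- k = 2: m = ±2 × 0.399 = ±0.798, so the share kept is 0.637 (= 2/π).
- k = 3, 4, 5: 0.793, 0.861, 0.897.

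**Step 2: variance of the effect, classes against linear age.** If age acts linearly, the ratio is (1 − kept × r²)/(1 − r²). For r = 0.3:
- two classes: (1 − 0.637 × 0.09)/0.91 = 0.9427/0.91 = 1.036
- three classes: (1 − 0.793 × 0.09)/0.91 = 0.9286/0.91 = 1.020

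The equivalent sample size is 300 divided by the ratio. The power column divides the noncentrality that gives 90% by the square root of the ratio.

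| r | classes | variance ratio | equivalent of 300 | power instead of 90% |
|---|---|---|---|---|
| 0.2 | 2 | 1.015 | 295.5 | 89.6% |
| 0.2 | 3 | 1.009 | 297.4 | 89.8% |
| 0.3 | 2 | 1.036 | 289.6 | 89.0% |
| 0.3 | 3 | 1.020 | 294.0 | 89.4% |
| 0.4 | 2 | 1.069 | 280.6 | 88.0% |
| 0.4 | 3 | 1.039 | 288.6 | 88.9% |

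Five of the six combinations lie between 0.9% and 3.9%; two classes at r = 0.4 give 6.9%. Outside this range, r = 0.1 costs 0.2 to 0.4% with two or three classes. The worst case tried, two classes at r = 0.5, costs 12.1% (power 86.5%).

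**Step 3: simulation.** 240 participants, 4,000 runs, no treatment effect, age with assumed mean 75 and SD 7 truncated at 60, cuts at 70 and 80, r = 0.3. The SD of the estimated effect was 0.1277 without age, 0.1245 with three classes and 0.1235 with linear age. The variance ratio of classes to linear age is (0.1245/0.1235)² = 1.016, close to step 2. Classes recovered (0.1277² − 0.1245²)/(0.1277² − 0.1235²) = 76% of the variance reduction that linear age achieved. The mean estimate was within 0.001 of zero, and the type I error was 4.9%, 5.2% and 5.2% respectively.

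**The case against.** The strongest case against reporting this is that the effect is tiny and rests on inputs the article does not give. That is largely right as to size. A headline such as 9% more variance, or 25 of 300 participants, needs two classes and age explaining 20% of the outcome variance at once: (1 − 0.637 × 0.20)/0.80 = 1.091, and 300/1.091 = 275.

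The linear-model arithmetic is also only a partial match to the planned analyses. The aims compare baseline with follow-up. In a group-by-time test, an effect of age on a participant's general level cancels, so only its association with change counts, and nothing in the article suggests that this is strong. The primary outcome is binary ("an increase of at least 1 point will indicate a success"), so residual-variance ratios do not carry over to it directly, nor to conversion to dementia.

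The covariate list is illustrative and open-ended, in a condensed article. A reader might infer that the cut points will be chosen after looking at the data. The documents do not support this: cut points are a detail that such an article commonly leaves to the full protocol or analysis plan. What remains open to criticism is the stated form, classes instead of years.

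A reader might also infer that age imbalance within classes makes the comparison invalid. It does not. Under randomisation such imbalance is ordinary sampling error, already reflected in the standard error.

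Finally, a straight line in age is itself an assumption. If the age effect is clearly non-linear, classes may lose less against a straight line than the table shows, so the fair comparator is then a quadratic or spline term. This bears on how age should be entered; it does not make grouping the better choice.

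**Conclusion.** The point holds as a minor one. The article names a coarser form of a probably prognostic covariate when the finer form is at hand, and gives no reason.

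The cost is precision only: about 1 to 4% of the variance of the effect over most of the assumed central range, about 7% at its unfavourable corner, and roughly one power point or less for correlations up to 0.3. It is probably less for change outcomes or once the baseline score is in the model. These sizes rest on an assumed correlation, assumed equal-sized classes and a roughly linear age effect. The documents support no claim of bias, false-positive inflation or serious loss of power from this choice.

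**What to change.** In the Statistical analysis section, replace age classes by age in years as a continuous covariate, and fix its functional form before the data are seen: linear, or with a quadratic or spline term if non-linearity is a worry. Keep age classes for descriptive tables.

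No new data, visits or participants are needed. The small price is an assumption about functional form, or one or two extra degrees of freedom to relax it. A quadratic uses two degrees of freedom in all, the same as three classes.

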#### Secondary outcomes

They include:the assessment of the intervention effects on lifestyle characteristics as well as psychological, functional and health status;the assessment of the intervention effects on mobility;the investigation of the conversion rate from MCI to dementia;the identification of biomarkers able to mirror the intervention effects.

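### The intervention-effect models may be adjusted for covariates chosen after the secondary results are seen, and post-randomisation values are not excluded

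*Protocol article*

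**What the plan says.** Statistical analysis states that a general linear model and "repeated measures ANOVA will be used to assess the intervention effects adjusted for confounding variables". The examples given are age class, gender, schooling, marital status and drugs. The list opens with *e.g.* and closes with "other variables that will emerge after analysis of secondary outcomes". The same sentence begins with a screening step: "Correlation analysis will be performed to evaluate the relationships among variables".

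Secondary outcomes defines where the extra variables would come from. It names "the assessment of the intervention effects on lifestyle characteristics as well as psychological, functional and health status", then mobility, conversion to dementia, and "the identification of biomarkers able to mirror the intervention effects".

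The primary outcome is binary. On the Corsi test, "an increase of at least 1 point will indicate a success". The only model linked to success or failure is the logistic regression in Sample size calculation, at a two-sided 5% level. The article does not say which model is the primary test. Allocation is made "using a randomisation list", 150 per arm.

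**The concern.** Two separate problems sit in one clause.

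**Timing.** A variable that emerges once secondary outcomes have been analysed is chosen with results in hand. This is more than detail left to an analysis plan: the article states the rule, and the rule depends on the data.

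**Kind of variable.** Secondary outcomes are things the intervention is meant to change, and the biomarkers are sought because they reflect its effect. A variable may emerge because treatment moved it. Adjusting for its follow-up value then removes part of the effect being estimated. The Discussion makes this concrete: it expects tango to act through postural control, balance and attention together with spatial memory, and the primary outcome is a spatial test. Because arm is randomised, a post-randomisation variable cannot be a confounder of the arm comparison.

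At stake are the adjusted effect estimates, which could be shrunk, reversed or selected.

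**Working it through.** The article gives no figure for the effect of adjustment, so there is none to reproduce.

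**Inputs from the article.** 300 randomised, 20% drop-out, two-sided 5%. Completers: 300 × 0.8 = 240, or 120 per arm.

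**Assumptions, not in the article.** A continuous outcome in SD units, as a general linear model would treat it; within-arm correlation r between covariate and outcome; shift d of the covariate caused by treatment, in the same favourable direction as the outcome; number of candidate covariates.

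**A. One post-randomisation covariate, no true total effect.** Bias = −r × d. SE = √(1 − r²) × √(2/120), where √(2/120) = 0.129. So SE = 0.123 at r = 0.3 and 0.112 at r = 0.5. Rejection = P(|Z + r·d/SE| > 1.96).

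| d | r | Bias (SD) | Rejection | of which favours intervention |
|---|---|---|---|---|
| 0.1 | 0.3 | −0.03 | 5.7% | 1.4% |
| 0.2 | 0.3 | −0.06 | 7.8% | 0.7% |
| 0.3 | 0.3 | −0.09 | 11.3% | 0.4% |
| 0.2 | 0.5 | −0.10 | 14.6% | 0.2% |
| 0.3 | 0.5 | −0.15 | 27% | 0.05% |

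In the last row, 0.15/0.112 = 1.34 and P(Z > 1.96 − 1.34) is about 27%. The share of rejections that go against the intervention runs from about three quarters in the weakest row to almost all in the strongest. False claims of benefit stay below the nominal 2.5% in every row.

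**B. Several post-randomisation covariates.** Take five, each correlated 0.3 with the outcome and with each other. Each coefficient is 0.3/(1 + 4 × 0.3) = 0.136, so the five sum to 0.682. If the true effect is 0.40 SD and each covariate also shifts by 0.40 SD, the adjusted estimate is 0.40 − 0.682 × 0.40 = 0.13 SD. In simulation (4,000 runs, 240 completers), rejection fell from 87% without these covariates to 17–19% when they were selected by significance or by correlation with the outcome.

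**C. Covariates unaffected by treatment, chosen after the results.** This covers the case where only baseline values are used. With no effect anywhere, take the smallest p-value among the models tried (simulation, 120 per arm):
- Unadjusted plus each single-covariate model: 10.5% (5 candidates, r = 0.3) and 11.0% (10 candidates, r = 0.25).
- Adding the model with all candidates: 11.7% and 14.0%.
- Adding models built up one covariate at a time: about 15% and 18%.

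**D. A mechanical selection rule with no effect anywhere.** Selecting covariates by their own significance gave 4.2%; selecting by correlation with the outcome gave 5.6%. Both are close to nominal.

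**E. No post-randomisation covariates and no selection.** Rejection under the null was 4.7–5.1% with mean estimate about 0; with a true 0.40 SD effect the estimate was 0.40.

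**The case against.** The strongest reply is that the added variables are called confounders and follow a list dominated by baseline traits. The specific aims compare baseline with each follow-up, so most secondary measures also have a baseline value. The clause may therefore mean baseline values of whichever measures prove relevant. That reading is possible. It removes the bias in A and B, but the choice would still be made after the results, and nothing in the article limits the additions to baseline.

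Three stronger conclusions that a reader might draw are not supported:
- *The plan adjusts for mediators.* It permits this; it does not state it.
- *The primary analysis is data-driven.* The clause belongs to the general linear model and repeated-measures ANOVA. Corsi success is binary and is linked only to logistic regression. The article does not say which model is primary, so an effect on that test is not shown; the calculations above use a continuous score.
- *A false claim of efficacy is likely.* When the covariate improves and correlates positively with the outcome, the bias runs against the intervention. Inflation from choosing among models needs an analyst who reports the most significant one, which the article does not describe.

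The sizes also rest on assumed correlations, shifts and candidate counts.

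**Conclusion.** The point stands in a conditional form. The article fixes a results-driven covariate rule for its adjusted intervention effects and does not exclude post-randomisation values.

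- If post-randomisation values are used, one covariate gives a bias of 0.03–0.15 SD and about 6–27% rejection with no true total effect, for assumed d of 0.1–0.3 and r of 0.3–0.5. The practical harm is mainly a masked benefit or an apparent harm.
- If only baseline values are used, that bias is absent, but choosing among models by result gives roughly 11–18% type I error with 5–10 candidates correlated 0.25–0.3 with the outcome. A mechanical rule with no effects stays near 5%.

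Neither size can be read from the article, and neither has been shown for the binary Corsi success test. The defect is worth correcting because a covariate set chosen after the results cannot credibly be defended later.

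**What to change.** In Statistical analysis:

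1. Delete the closing phrase on emerging variables and the *e.g.* that leaves the list open.
2. Fix the adjustment set before any outcome data are seen, limited to baseline variables: those already listed (gender, age, marital status, schooling, and drug use as recorded at baseline), plus the baseline value of the outcome where applicable. No listed variable needs to be dropped.
3. Apply the same rule to the logistic model for Corsi success.
4. Label any model that includes a variable measured after randomisation as exploratory mediation analysis, separate from the estimate of the intervention effect.

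The cost is a few words in one section. It needs no new data and no change to the sample size, and mediation questions can still be studied under their own label.
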